### Trial design

The study is a two-armed randomized controlled trial examining the primary outcomes of adolescent-caregiver relationship, adolescent intention to have sex and adolescent adaptive/maladaptive functioning at 12 months post intervention. The trial is being conducted at two study sites on the Navajo Nation with Navajo girls ages 10–14 and their female caregiver. Randomization will be performed with a stratified block randomization sequence to ensure a 1:1 allocation of study conditions within each of the two study sites Fig. 1.

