### Randomization and sample size

This study will use a 1:1 randomized controlled trial design; the unit of randomization will be the individual dyad. Unique participant identification numbers will be used to randomize individual dyads to one of two study groups: intervention or control. Stratified block randomization, using random block size will be used to ensure a 1:1 allocation of study conditions across the two study sites. The sequence will be generated by the program evaluation via STATA and will not be shared with study staff who enroll participants.. Independent Evaluators will enroll participants and reveal study group after the participants complete the baseline assessment. The study assignments are sequentially numbers in sealed envelopes that are only opened at the time of randomization. No blinding will occur.

Sample size and statistical power estimates are predicated on 2 primary hypotheses: 1) that those randomized to the AB intervention will have improved parent-adolescent communication compared to the control group, and 2), that those randomized to the AB intervention group will have a higher proportion of participants who report they intend to abstain from sex.

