The sample size of 410 dyads (*n* = 205 per study arm) will be sufficient to detect a 0.3 difference between study groups, with 90% power and 0.05 significance level, on the communication scale at 12 months post-intervention (estimating a mean score (SD) of 2.81(0.85) in the control group). This same sample size will be sufficient to detect an 18% between-group difference, with 80% power and 0.05 significance level, in the proportion of participants who report intention to abstain from sex at 12 months post-intervention (estimating 50% of the control group to report intention to abstain from sex at 12 months post-intervention). This sample size will also be able to detect meaningful differences in other key confirmatory research question outcomes at 12 months post-intervention. The following presents minimum detectable differences between the intervention and control groups with at least 80% power, given the assumptions listed above: 0.39 between-group difference in internalizing behaviors (estimating a mean score (SD) of 5.23 (0.99) in the control group), and 0.25 between-group difference in externalizing behaviors (estimating a mean score (SD) of 2.04 (0.63) in the control group). All estimates assume 10% attrition between enrollment and program completion and a 25% attrition rate between program completion and the 12 month follow-up time point.

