### Statistical analysis

The between study group equivalence of participant characteristics and outcome measures at baseline will be compared using Chi-squared tests (dichotomous/categorical data) and t-tests (continuous data). Study hypotheses related to the confirmatory questions will be initially tested under an “intent-to-treat” model in which data are analyzed according to treatment assignment at randomization. We will then conduct “completer analyses” on those subjects completing at least two-thirds of intervention sessions. Intervention impact will be evaluated by comparing primary study outcomes between intervention and control groups across the three time points: baseline, 6 months and 12 months post-intervention. Initially, summary scores of outcomes will be stratified by participation in the intervention versus control groups and by time point, and will be compared using chi-square tests (binary or categorical outcomes), t-tests and analysis of variance (continuous outcomes). Generalized linear mixed effects models (GLMM) accounting for within-group correlation across longitudinal data will then be applied. Outcomes will be modeled as a function of group assignment and time since intervention. The association between outcomes and time will be explored visually using scatterplots and lowess smoothers. Restricted cubic splines will be added to reflect deviations from linearity.

If siblings enter the study, they will be randomized to the same intervention group to limit contamination. In this case, analyses will be adjusted to take into account intra-sibling correlation as well. Additionally, sensitivity analyses will be conducted including and excluding siblings to examine the impact on study results. Missing data will be handled as follows: 1) identify erroneous data, 2) document reason(s) for missing and erroneous data to inform model development; 3) compare demographic characteristics of those who dropped out and those who did not to compare if data is missing at random; and 3) conduct sensitivity analysis to compare inferences that are based on different plausible reasons for missingness. Navajo and Hopkins investigators will collaborate with community partners in data interpretation to assure accuracy, cultural acceptance and relevance.

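### Read literally, the mixed model has no term for the 12-month group difference that the trial is powered on, and the plan does not say which analysis decides

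*Protocol article*

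**What the plan says.** Three parts of the protocol article bear on this.

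- **Time point.** Trial design lists the primary outcomes as the adolescent-caregiver relationship together with "adolescent intention to have sex and adolescent adaptive/maladaptive functioning at 12 months post intervention". Randomization and sample size powers the trial on a difference "on the communication scale at 12 months post-intervention" and does the same for intention to abstain from sex.
- **Analysis.** Statistical analysis compares the arms "across the three time points: baseline, 6 months and 12 months post-intervention". Summary scores are first compared by arm and time point with chi-square tests, t-tests and analysis of variance. After that, "Generalized linear mixed effects models (GLMM) accounting for within-group correlation across longitudinal data will then be applied", and "Outcomes will be modeled as a function of group assignment and time since intervention". Restricted cubic splines may be added for non-linearity in time.
- **Randomisation.** The evaluators "reveal study group after the participants complete the baseline assessment". On stratification: "Stratified block randomization, using random block size will be used to ensure a 1:1 allocation of study conditions across the two study sites".

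The section names no group-by-time term, baseline covariate, common baseline mean or 12-month contrast. It does not say which of the two analyses tests the primary hypotheses.

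**The concern.** Baseline is measured before the arm is known, so the expected arm difference there is zero. If baseline is an outcome row and the model has only a group term and a time trend, the single group coefficient is a weighted average of the arm differences at baseline, 6 and 12 months. That is not the 12-month difference, and the zero at baseline pulls it down. Baseline is also the most complete visit, so attrition increases its weight. Splines change only the shape of the common time trend and leave the dilution in place.

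An analyst who implements the sentence as written would report an effect smaller than the 12-month effect and test it with less power than a direct 12-month comparison. With the by-visit tests also in the plan, the same hypothesis has two analyses with different targets and no rule for choosing between them.

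**Working it through.** **Inputs from the article (Randomization and sample size).** 205 per arm; difference 0.3; SD 0.85; 90% power; significance level 0.05; attrition of 10% and then 25%. Expected number at 12 months: 205 × 0.90 × 0.75 = 138 per arm.

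**Assumed, because the article does not give them.** Within-person correlation ρ from 0.3 to 0.7, equal between all visits; the number present at 6 months; the time course of the effect.

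**The plan's own figure.** The article states: "The sample size of 410 dyads (*n* = 205 per study arm) will be sufficient to detect a 0.3 difference between study groups". The required number per arm at 12 months is 2 × 0.85² × (z_α + z_β)² / 0.3².

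- One-sided 0.05: 16.06 × (1.645 + 1.282)² = 138; 138 / 0.675 = 205 per arm, or 410 in total. This matches.
- Two-sided 0.05: 16.06 × (1.960 + 1.282)² = 169; 169 / 0.675 = 251 per arm, or 502 in total. This does not match.

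The design calculation is therefore a simple two-group comparison at 12 months. Power below is two-sided unless stated.

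**Direct 12-month comparison, 138 per arm.** SE = 0.85 × √(2/138) = 0.102; 0.3 / 0.102 = 2.93; power = Φ(2.93 − 1.96) = 83%.

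**Group coefficient with group and time terms only.** Let c_k be the number per arm seen at exactly the first k visits. The weight of visit j is w_j = Σ over k ≥ j of c_k / (1 + (k − 1)ρ). The coefficient is Σ w_j δ_j / Σ w_j, where δ_j is the arm difference at visit j. Its SE is √(2 × 0.85² / Σ w_j).

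*Complete data, 138 at each visit.* The weights are equal.

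- Sustained effect: (0 + 0.3 + 0.3) / 3 = 0.20.
- Linear build-up: (0 + 0.15 + 0.3) / 3 = 0.15.
- SE = 0.075, 0.084 and 0.092 for ρ = 0.3, 0.5 and 0.7.

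*With dropout, 205 / 160 / 138 per arm (160 assumed), ρ = 0.5.*

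- c = 45, 22, 138.
- w at 12 months = 138/2 = 69; at 6 months = 69 + 22/1.5 = 83.7; at baseline = 83.7 + 45 = 128.7; sum 281.3.
- Sustained coefficient = 0.3 × (69 + 83.7) / 281.3 = 0.163.
- SE = √(1.445 / 281.3) = 0.072; power = Φ(2.27 − 1.96) = 62%.

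| Effect at 0, 6, 12 months | Numbers per arm | Coefficient | Power at ρ = 0.3 / 0.5 / 0.7 |
|---|---|---|---|
| 0, 0.3, 0.3 | 138/138/138 | 0.20 | 76% / 67% / 59% |
| 0, 0.3, 0.3 | 205/160/138 | 0.17 to 0.16 | 73% / 62% / 54% |
| 0, 0.15, 0.3 | 138/138/138 | 0.15 | 52% / 44% / 37% |
| 0, 0.15, 0.3 | 205/160/138 | 0.12 to 0.11 | 47% / 38% / 32% |

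**Sensitivity to the 6-month number.** With 184 present at 6 months (no loss between program completion and 6 months), the sustained coefficient is 0.18 to 0.17 and power 79% to 62%. With 138 present (all loss by then), they are 0.16 to 0.14 and 67% to 46%.

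**Sensitivity to sidedness.** With one-sided 0.05, the direct comparison has Φ(2.93 − 1.645) = 90%. The group coefficient (sustained effect, dropout as in the table, ρ = 0.5) has Φ(2.27 − 1.645) = 73%. The shortfall remains.

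**12-month contrast with a common baseline mean.** The estimate is 0.30. With complete data, SE = 0.102 × √(1 − ρ²), which gives power of 87%, 92% and 98% for ρ = 0.3, 0.5 and 0.7. With the dropout above the figures are 87%, 93% and 99%.

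The binary intention outcome was not computed. Dilution there runs in the same direction on the logit scale.

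**The case against.** Two arguments on the other side are strong.

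First, the sentence lists predictors and is not a model equation. Saying that outcomes are a function of group and time does not exclude a group-by-time term, and a condensed article commonly leaves interactions, covariates and contrasts to a fuller document that is not shown here. A reader might infer that the confirmatory model definitely contains main effects only. The article does not establish that, and it never attaches the word confirmatory to the mixed model; it uses the word for the research questions and the intent-to-treat principle.

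Second, the plan does contain an undiluted 12-month comparison, in the tests by time point. A reader might infer that a true 0.3 effect will be reported at about half its size. That would follow only if the group coefficient were the sole reported estimate. Half is also near the low end of a range that rests on assumed correlation, time course and 6-month dropout. An effect absent at 6 months and present only at 12 would be diluted further, but Objectives hypothesises effects at both times.

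Some related matters are not errors. The unadjusted test is valid, though less efficient than one that uses the baseline score. Covariates such as site are often specified in the analysis plan. The splines do not cause the dilution.

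What remains is that the article names baseline as an outcome visit, names only group and time as predictors, and does not say which analysis decides. Nothing in its text supplies the missing 12-month term.

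**Conclusion.** The point holds as a conditional one: following the stated model literally answers a different and weaker question than the 12-month one on which the trial rests. Under a sustained 0.3 effect the group coefficient is about 0.16 to 0.20 (53% to 67% of the effect), with roughly 54% to 76% power. Varying the 6-month number between its extremes widens the power range to 46% to 79%. A linear build-up gives 0.11 to 0.15 and 32% to 52%. The by-visit test has about 83%, and a 12-month contrast with a common baseline mean has 87% to 99%.

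The direction follows from the zero expected difference at baseline and does not depend on the assumptions. The size does: it rests on the assumed correlation, time course and 6-month retention. The article does not support the conclusion that the trial will report a diluted result, only that its wording permits one and names no deciding analysis.

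**What to change.** Replace the sentence on the model terms with wording to this effect:

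- Visit is categorical (baseline, 6 and 12 months), with group-by-visit terms after baseline and a baseline mean common to both arms. Adjusting post-baseline outcomes for the baseline value is an acceptable alternative.
- Site, the stratification factor, is a fixed effect.
- The group contrast at 12 months is the primary estimate for both the communication and the intention outcomes.
- The t-tests and chi-square tests by time point are descriptive.

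With three analysis visits, categorical time makes the splines unnecessary. Adding the immediate post-program visit and adjusting for age are optional.

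The cost is a change of analysis wording. The outcomes are already scheduled at every visit and site is known from randomisation, so no data collection or design feature changes. If an analysis plan already contains these terms, the article's sentence need only be brought into line with it.

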#### Study staffing

This study is being conducted at two study sites on the Navajo Nation. The Center has had a physical office and has conducted projects in partnership with the Navajo Nation for over 30 years. Each site has two family health coaches (FHCs), one independent evaluator (IE) and one site coordinator. Other members of the study team, including the principal investigator, program manager, program coordinator and evaluator, are located at the Center’s administrative office in Baltimore, Maryland. The field manager is located in Arizona near the Navajo Nation. All members of the study team are full-time Johns Hopkins employees and are thoroughly trained in human subjects research prior to working with participants. Members of the Baltimore team and the field manager make frequent trips (at least bi-annual) trips to the study sites to conduct training and quality assurance.

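### Randomization is stratified by site but the stated outcome model names only group and time, a small and avoidable loss of precision for continuous outcomes compared at a single time point

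*Protocol article*

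**What the plan says.** The Trial design section states: "Randomization will be performed with a stratified block randomization sequence to ensure a 1:1 allocation of study conditions within each of the two study sites". The Randomization and sample size section repeats this: "Stratified block randomization, using random block size will be used to ensure a 1:1 allocation of study conditions across the two study sites". Site is the only stratification factor named, and the dyad is the unit randomized.

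The Statistical analysis section begins with chi-square tests, t-tests and analysis of variance on summary scores, split by arm and time point. It then moves to the main model: "Generalized linear mixed effects models (GLMM) accounting for within-group correlation across longitudinal data will then be applied". The model terms follow: "Outcomes will be modeled as a function of group assignment and time since intervention". Splines may be added for time. If siblings enrol, "analyses will be adjusted to take into account intra-sibling correlation as well". Site is named in none of these steps.

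On what site stands for, the Study staffing section says: "Each site has two family health coaches (FHCs), one independent evaluator (IE) and one site coordinator". Table 2 shows that the adolescent relationship outcomes, including communication, are collected by interview, while sexual intentions are self-reported. The limitations in the Discussion add that one evaluator follows each dyad from baseline through every follow-up.

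**The concern.** Stratified blocks balance the arms within each site, so a site difference contributes almost nothing to the true sampling variance of the arm comparison. An analysis without site still counts that difference as residual error. The reported standard error then exceeds the true one, and the test rejects less often than its nominal level.

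Sites could plausibly differ here. Each has a single evaluator who interviews the adolescents on the relationship outcomes, and each has its own coaches, so site carries interviewer and delivery differences as well as community differences. What is at stake is power that the randomization has already secured, on an outcome used to set the sample size.

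**Working it through.** **Inputs from the protocol (Randomization and sample size).** 205 dyads per arm; communication difference 0.3, SD 0.85, alpha 0.05, stated power 90%; attrition 10% and then 25%. Dyads per arm at 12 months: 205 × 0.90 × 0.75 = 138.4.

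**Assumptions.** Two-sided test (sidedness is not stated), normal approximation, equal-sized sites, 0.85 taken as the total SD, and a site difference *d* of 0.25 to 0.5 within-site SDs. The protocol gives no figure for *d*.

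**The plan's own figure.** Standard error = 0.85 × √(2/138.4) = 0.1022. Power = Φ(0.3/0.1022 − 1.96) = 83.5% two-sided. With a one-sided critical value of 1.645 it is 90.2%, which matches the stated 90%. The two-sided value is the baseline below. The sidedness question is separate from this point.

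**Inflation of the standard error.** With half the dyads at each site, the site difference adds *d*²/4 to a within-site variance of 1. Reported SE ÷ true SE = √(1 + *d*²/4).
- *d* = 0.25: √1.0156 = 1.008, or 0.8% too large.
- *d* = 0.5: √1.0625 = 1.031, or 3.1% too large.

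**Actual type I error**, 2[1 − Φ(1.96 × ratio)].
- *d* = 0.25: 4.8%.
- *d* = 0.5: 4.3%.

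**Power for communication.** Under stratified allocation the estimate varies with the true standard error in both analyses; only the standard error used in the test differs. Without site, power is Φ((0.3 − 1.96 × 0.1022)/true SE). With site, it is Φ(0.3/true SE − 1.96).
- *d* = 0.25, true SE 0.1014: 83.7% without site, 84.1% with site, a gain of 0.4 points.
- *d* = 0.5, true SE 0.0991: 84.3% without site, 85.7% with site, a gain of 1.4 points.

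**Simulation check** (276 analysed, 8,000 runs, within-site SD 1). At *d* = 0.5 the mean standard error was 0.1240 without site and 0.1203 with it, and type I error was 0.041 against 0.048. With no site difference the two analyses agreed (0.050 each).

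**Change from baseline.** In the same simulation, the arm comparison of change with a constant site difference had type I error 0.048, 0.048 and 0.050 at *d* = 0, 0.5 and 1.0. The site difference cancels.

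**Binary intention outcome.** Take 50% against 68% (the stated 18-point difference), 138.4 per arm, and an assumed site log-odds difference of 0.5.
- Without site: log odds ratio ln(0.68/0.32) = 0.754; SE = √[1/(138.4 × 0.25) + 1/(138.4 × 0.2176)] = 0.249; z = 3.02.
- With site: log odds ratio 0.765, SE 0.251, z = 3.04.

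The standard error does not shrink, and the test statistic hardly moves.

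**The case against.** **The article is condensed, and an analysis plan that is not shown may add site.** That is possible, and the article does not say that its list of terms is closed. But it does state the model terms and goes as far as splines and sibling correlation, while leaving out the one factor used to stratify. The correction applies to a stated model.

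**The longitudinal model may be read as a change contrast.** Baseline is among the time points compared, so a group-by-time effect is a natural estimand. A constant site difference cancels there, including a stable evaluator effect, since each dyad keeps the same evaluator. This stands as a limit on the point. The text names no interaction, however; the first-step tests compare arms at each time point, and the sample size is justified on a between-arm difference at 12 months. For those comparisons the loss remains, as it does if the site difference shifts over time.

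**The binary outcome gains nothing useful.** This also stands. Intention is self-reported, so the interviewer argument does not reach it, and a logistic model with site has no smaller standard error.

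**Other features may act the other way.** Group sessions in cohorts of 7 to 12 dyads could make the stated standard errors too small. The net direction of all such errors is not established; this point isolates stratification.

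A reader might infer that every confidence interval in the trial is too wide, or that one evaluator per site biases the arm comparison. Neither follows. The first fails for change contrasts and for the logistic model. The second fails because arms are balanced within site, so each site's evaluator sees both arms.

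**Conclusion.** The point holds in a limited form and is minor. The stated analysis leaves out the only stratification factor. For continuous outcomes compared between arms at a time point, that costs 0.8% to 3.1% in the standard error and about 0.4 to 1.4 points of power on communication, if the sites differ by 0.25 to 0.5 SD. That range is an assumption; with no site difference the cost is zero. The figures also assume equal sites, a two-sided 0.05 level and both attrition steps. The error is conservative, so a reading that the trial's validity or false-positive rate is at risk is not supported.

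**What to change.** In the Statistical analysis section, add study site, identified as the randomization stratum, as a fixed effect alongside group assignment and time since intervention. State that the unadjusted t-tests, analysis of variance and chi-square tests are descriptive. This takes one phrase and one sentence. Site is already known from randomization, the term uses one degree of freedom, and nothing changes for participants or data collection. For the binary intention outcome the reason to include site is consistency with the design, since no gain in precision should be expected.

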## Discussion

This study protocol presents one of the first RCTs of a program designed by and for a Native community to promote protective factors associated with delayed substance use and sexual initiation among young girls.

This study has many strengths. First, as previously noted, AB was designed in consultation with Navajo cultural specialists and was shown to be culturally appropriate and acceptable in the pilot trial (Chambers 2021). Public health interventions with roots deriving from cultural teachings have brought inclusion and participant connection with the lesson content, thus solidifying the importance of integrating culture as the foundation for prevention programs specific to AI communities. Further, the program is designed specifically for female adolescents and draws on the traditional matrilineal society of the Navajo. Across ethnicities, female adolescents have distinct patterns and processes for underage substance use and sexual risk-taking that are different from male adolescents [59, 60]. Some of these differences include females being more likely than males to use substances due to low self-esteem [61, 62], and to be offered substances in private settings by female relatives [63, 64]. Also, lack of family support is a stronger risk factor for substance use and sexual initiation among Native female adolecsents than male adolescents [62]. Thus, a gender specific approach is a strength of this program.

Second, there is substantial evidence that parental involvement in teen pregnancy and substance use prevention programs is advantageous [65–67]. However, researchers have cited the lack of parental involvement in sexual health promotion programming as a gap in efforts to prevent teen pregnancy. They conclude that by providing the parent and adolescent the same health promotion and sexual risk prevention information, the parent is informed of what the adolescent is learning and can reinforce these teachings at home [68]. Given this, inclusion of a caregiver in this program alongside the adolescent is a major strength and may enhance and help to sustain positive program impact long after the completion of the program. Next, this study will assess the impact of the program on individual-level factors of both the caregiver and adolescent. This will not only allow for the understanding of program impacts on both caregiver and child, but will also allow the study team to better understand, 1) how adolescent and caregiver outcomes and risk/protective factors are associated with each other, and 2) how changes in adolescent and/or caregiver outcomes mediate change in outcomes in the other member of the dyad.

Third, the study builds on more recent research highlighting the importance of primary prevention programs delivered during early adolescence, when adolescents are less likely to have initiated risk-taking behaviors such as substance use and sex [68, 69]. In addition, the AB program is designed to simultaneously impact co-occurring risk behaviors that impact Native adolescents and communities at disproportionate rates. If AB is efficacious at reducing both sets of risk behaviors, it will fill a gap in the literature calling for evidence based interventions (EBIs) that work across domains and are not specific to one risk behavior (e.g. risks for substance use or early sex). Programs such as AB may be particularly beneficial for Native and other under-resourced populations for whom few comprehensive EBIs exist.

This study also has limitations. First, all outcomes are measured via self-report and/or via interview. While self-report is the most widely used methodology to assess behavior change, it is not without biases. There are also potential biases in interview administration, such as… [70]. However, steps have been taken to reduce potential biases. The IEs are highly trained in evaluation administration and human subjects research and will not deliver any part of either AB program or condition non-monetary gifts, limiting potential evaluator bias. Other methods to reduce bias include: 1) all IEs will be Native women from the local community, 2) the same IE will conduct the baseline and all follow-up assessments for each dyad, 3) all interviews will be conducted in person (vs. some in person and some via telephone/video call), and 4) the most sensitive questions focused on actual behavior and behavioral intention are conducted via self-report (not interview).

Another limitation is that the follow-up time period is only 1 year. Since adolescents are 10–14 years of age when enrolling in this program, we do not expect a large proportion of adolescents to initiate substances or have sex by the 12 month follow-up timepoint. Thus, we do not expect to have adequate power to assess impact of AB on actual behaviors. However, we will have power to assess the impact of AB on behavioral intention. Studies indicate there is a strong, positive association between intention to abstain from sex and delayed sexual initiation [71]. Further, we will assess key protective factors that are associated with delayed sexual initiation and substance use among Native and non-Native adolescents [19, 23, 71].

Third, there is potential for some contamination between control and intervention groups, as this study will be conducted in a small communities where many families know each other. To limit contamination, we will individually randomize dyads and assign siblings to the same randomization group.

To our knowledge, this is the first RCT of a culturally grounded primary prevention program for teen pregnancy and substance use among female Native adolescents and their female caregivers. If AB proves efficacious, there will be a program for Native families that promotes protective factors associated with delayed substance use and sexual risk taking. Additionally, we may deepen our understanding of the relationship between adolescent and caregiver individual and family level factors, how each of these contribute to risk taking behaviors among Native adolescents, and how shifts in adolescent individual level factors influence caregiver outcomes and vice versa.

